### 6.2 Participant selection

Interview invitation will be provided when participants complete the pilot RCT of the FZHFZY Trial. We will maximise participant diversity in terms of age, gender, civil state, education level, employment status, geographical location, history and severity of psoriasis vulgaris, comorbidity, response to treatment, AEs, treatment adherence and satisfaction scores from the pilot RCT without knowing their group allocation. Within this context, we seek to achieve diversity in the sample to ensure that a broad range of views, characteristics and experiences of participation will be obtained [57, 58].

### 6.3 Data collection

Data collection will be performed through qualitative, semi-structured interviews with an interview guide of open-ended questions. It will be conducted within 4 weeks after completing the pilot RCT. During the interviews, participants will be encouraged to speak freely about their efficacy and safety

evaluation and experience with CHM external application for psoriasis vulgaris. Subsequently, they will primarily be asked about their experiences with and perspectives on the entire pilot FZHFZY RCT, and the acceptability of the pilot RCT. We will use the interview guide and questions flexibly to respond to the participant's pace and experience. It means each participant will be encouraged to tell the story in the best suitable way. The duration of the interviews will range from one to one and half hours. We will make field notes during each interview and summarise these at interview completion. With participants' permission, interviews will be audio-recorded and transcribed verbatim.

An interview guide (Table 4) will be developed based on a review of the relevant academic literature addressing similar questions and psoriasis patients' experience of using Chinese herbal medicine [59-63].

**Table 4** Interview guide and interview questions

| Interview guide                                                                                                       | Interview questions                                                                                                                                                                                                                                                                                                                                                                                                                                                                                                                                                                                                                                                             |
|-----------------------------------------------------------------------------------------------------------------------|---------------------------------------------------------------------------------------------------------------------------------------------------------------------------------------------------------------------------------------------------------------------------------------------------------------------------------------------------------------------------------------------------------------------------------------------------------------------------------------------------------------------------------------------------------------------------------------------------------------------------------------------------------------------------------|
| 1. In the pilot RCT, the efficacy evaluation and experience of CHM external application for psoriasis vulgaris | 
 
➤ Why did you participate in the clinical trial?
 
➤ What did you expect from the treatment at the start of the trial?
 
➤ What issue caused by the psoriasis you expect to be resolved through the trial?
 
➤ What is your overall impression about the CHM bath therapy?
 
➤ Anything in particular that you liked or found helpful?
 
➤ Anything you did not like or found less helpful?
 
➤ To what extent did the therapy match your expectations—why (not)/how (not)/in what ways?
 
➤ How well the therapy helped you with the issues that you wanted to be resolved?
 
 |
| 2. In the pilot RCT, the safety evaluation and experience of CHM external application for psoriasis vulgaris   | 
 
➤ How to evaluate the overall safety of the trial?
 
➤ In the clinical trial, what safety concerns did you have?
 
                                                                                                                                                                                                                                                                                                                                                                                                                                                                                                       |
| 3. Acceptability of the pilot RCT                                                                              | 
 
➤ Are you satisfied with the effects of the treatment regimen? If yes, why? If not, why?
 
➤ Will you choose the CHM bath therapy again in the future? If yes, why? If not, why?
 
➤ Will you recommend this therapy to others? If yes, why? If not, why?
 
                                                                                                                                                                                                                                                                                                                                                       |

|                                                                      |                                                                                                                                                                                                                                                    |
|----------------------------------------------------------------------|----------------------------------------------------------------------------------------------------------------------------------------------------------------------------------------------------------------------------------------------------|
| 4. Clinical uncertainties associated with a large-scale trial | 
 
➤ What is your experience of administration instructions and precautions of FZHFZY granules?
 
➤ Experience of bath temperature/ CHM bath duration/ frequency/ treatment duration/ visits
 
 |
|----------------------------------------------------------------------|----------------------------------------------------------------------------------------------------------------------------------------------------------------------------------------------------------------------------------------------------|

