#### **4. Trial design**

The FZHFZY Trial consists of two main parts. For the quantitative and qualitative components, we will collect data concurrently and analyse data sequentially, with quantitative data informing our sampling of qualitative interviews for analysis.

- Part 1: This will be a two-arm, parallel, randomised, placebo-controlled, double-blind, pilot trial. In all, sixty eligible participants will be randomised at a 1:1 ratio to receive eight weeks' treatment of either CHM FZHFZY granules as a bath therapy plus 10% urea cream, or placebo granules plus 10% urea cream, with a 12-week follow-up phase.
- Part 2: This will be an embedded qualitative study with the above-mentioned pilot RCT. The primary source of data collection will be semi-structured interviews via face to face. The data will be analysed through thematic analysis.

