#### 5.3.2 Placebo

Placebo consisting of starch with no active ingredients will be made by the same manufacturer to match the FZHFZY granules as closely as possible, in terms of their colour, appearance, and smell. The colour will be made identical by adding artificial pigment whilst the taste will be adjusted by adding a medicine intermediate. The administration instructions and precautions for the FZHFZY formula and placebo will be identical.

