#### 6.5 Qualitative data analysis

For analysing qualitative data, thematic analysis based on an inductive approach will be conducted [65, 66]. Thematic analysis is described as a flexible approach to analysis that has theoretical freedom, so it is possible to apply a constructivist paradigm and an inductive approach to arrive at a detailed interpretive account of the data [66]. There are six phases of the analytical approach [67]: 1) Familiarization: read and re-read transcripts and field notes to become familiar with the data; 2) generate codes; 3) construct candidate themes; 4) revise themes; 5) define themes; and (6) produce the report. A series of themes and sub-themes will be generated following this process based on grounded theory. All the interviews will be transcribed in full and verbatim by using the original language (Chinese). Transcripts will be de-identified, coded and uploaded to NVivo 12 software (QSR International Version 12, 2018) for data management and data coding [68]. Transcripts will be coded line by line to label themes. Preliminary data analysis will be conducted to determine if the interview guide needs to be revised after every interview.

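### Interviews take in both arms blind to allocation, but the guide labels the accounts as evaluation of CHM and the thematic analysis does not provide for linking transcripts to arm

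*Protocol*

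**What the plan says.** The pilot RCT allocates equally: "sixty eligible participants will be randomised at a 1:1 ratio to receive eight weeks' treatment" (Protocol section 4). The control product is inert: "Placebo consisting of starch with no active ingredients will be made by the same manufacturer to match the FZHFZY granules" (5.3.2). How it is used does not differ between arms: "The administration instructions and precautions for the FZHFZY formula and placebo will be identical" (5.3.2).

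Anyone who completes the RCT may be interviewed, with no restriction by arm (synopsis; 6.1). Section 6.2 seeks diversity on a list of characteristics that includes treatment response, adverse events, adherence and "satisfaction scores from the pilot RCT without knowing their group allocation". Between 24 and 30 interviews are expected, and saturation sets the final number (6.4).

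Section 6.3 says that interviewees will talk about their efficacy and safety "evaluation and experience with CHM external application for psoriasis vulgaris". In Table 4, the headings of blocks 1 and 2 give the same label to the efficacy and safety material. Two evaluative items name the product: "What is your overall impression about the CHM bath therapy" in block 1 and "Will you choose the CHM bath therapy again in the future? If yes, why? If not, why" in block 3. Two items in block 4, on the granule instructions and on bath duration, also name FZHFZY or CHM.

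On analysis, section 6.5 describes one inductive thematic process: "A series of themes and sub-themes will be generated following this process based on grounded theory". Nothing in sections 6.1 to 6.7 mentions the allocated arm at the analysis stage.

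**The concern.** Interviewing both arms and sampling blind are sound. The difficulty is the label put on the answers. A placebo user's account of symptom relief, irritation, satisfaction or willingness to bathe again describes a starch bath. The plan files it under evaluation of CHM, and no step tells the analyst or reader which accounts came from FZHFZY users.

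The synopsis gives the qualitative outcome two parts: how patients judge and accept the treatment, and how they experienced the trial as a whole. The first part is at stake. A theme about perceived benefit or dislike could come mainly from placebo users and still be read as a finding on FZHFZY. The pilot's results are meant to improve the design of the full-scale study (sections 2 and 3.1).

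**Working it through.** **1. What each part of the guide asks**

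Table 4 has 8 + 2 + 3 + 2 = 15 items.

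| Part of the guide | Names CHM or FZHFZY? | Does the arm matter for the answer? |
|---|---|---|
| Headings of blocks 1 and 2 (efficacy, safety) | Yes | Yes |
| Overall impression (block 1) | Yes | Yes |
| Choosing it again (block 3) | Yes | Yes |
| Granule instructions; bath duration (block 4) | Yes | Little: instructions are identical |
| Other 11 items | No: they speak of the treatment, the therapy or the trial, or are general | Varies |

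So 4 of 15 items name the product, and two of those four are evaluative. Both safety questions ask about the trial. The CHM label on the safety material comes from section 6.3 and the block heading.

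**2. The plan's own figure**

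Section 5.9.1 aims for 60 from a minimum of 50 with 15% loss. 50 / (1 − 0.15) = 58.8, rounded up to 59, which agrees with 60 to within one participant. With 15% loss, 60 × 0.85 = 51 complete.

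**3. Expected placebo share of the interviews**

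With 30 of 60 on placebo, the expected number is n × 30/60:
- n = 24: 12
- n = 30: 15

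If selection were unrelated to arm, the number of placebo users would follow a hypergeometric distribution. The rows with 51 completers assume how the losses fall, because the protocol gives no figure by arm.

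| Placebo users / pool | Expected share | Central 95% range, n = 24 | Central 95% range, n = 30 |
|---|---|---|---|
| 30 / 60 | 50% | 8–16 (33–67%) | 11–19 (37–63%) |
| 25 / 51 | 49% | 8–15 | 11–18 |
| 26 / 51 | 51% | 9–16 | 12–19 |
| 21 / 51 (uneven loss) | 41% | 6–13 | 9–16 |
| 30 / 51 (uneven loss) | 59% | 11–18 | 14–21 |

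The chance of interviewing no placebo user is below 1 in 100 million in every row. These ranges illustrate and do not predict. Section 6.2 selects on response, adverse events, adherence and satisfaction, which may differ by arm.

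**4. Can the plan as written separate the accounts?**

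No step in section 6.5 does so, and section 6.4 judges saturation without reference to arm. The means exist: the RCT uses unique study codes with a separate reference table (5.8), and recordings and transcripts carry code numbers (6.7).

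**The case against.** **Pooling is not stated.** A reader might infer that the protocol commits to one pooled set of themes. It does not: section 6.5 neither promises pooled reporting nor rules out a split after unblinding. This objection stands. What can be said is that linkage to arm is not provided for, while the wording assigns every account to CHM.

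**The interviews are not the efficacy evidence.** A reader might infer that half of the trial's evidence on CHM comes from placebo users. The documents do not support that. Efficacy and safety are measured in the RCT (5.6.2, 5.6.3), and section 5.9.2 compares outcomes between groups. Compliance and acceptability are also measured quantitatively (5.6.1).

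**Interviewees may not be told that they had CHM.** The guide could be read as telling each interviewee this. Section 5.3.3, addressed to both groups, uses the CHM bath as a label for the bath in either arm. Interviews are transcribed in Chinese (6.5), so the spoken wording is not shown. Interviews also follow RCT completion, so they cannot alter that participant's trial outcomes or blinding assessments.

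**Placebo users are valid informants.** This is true for visits, bath temperature, duration, frequency and the trial as a whole, and those themes can be pooled.

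**The guide may change.** It is to be used flexibly (6.3), piloted (6.6) and reviewed after every interview (6.5). That could improve the wording but would not supply an arm label at analysis.

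**Conclusion.** The point holds for the treatment-specific part of the interviews. As written, placebo users' accounts of effect, safety, satisfaction and reuse would be reported as evaluation of CHM, and nothing planned would let a reader tell them apart. The expected share is about half, which rests only on 1:1 randomisation and selection unrelated to arm. A range of a third to two thirds should not be read as a forecast: it is the random-draw range for 24 interviews, and purposive sampling among completers could move the share either way. The conclusion does not depend on the exact share.

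The RCT's between-arm analyses and the themes on procedures and trial experience are unaffected. The change is still worth making before the first interview, because question wording cannot be repaired afterwards.

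**What to change.** - **Wording.** In section 6.3, the headings of Table 4 blocks 1 and 2, and the four items that name CHM or FZHFZY, use a neutral term such as *the study bath*.
- **Conduct.** Keep selection, interviewing and coding blinded, as planned.
- **Analysis.** Add to section 6.5 that, after the trial is unblinded, transcripts will be linked to allocation through the study codes. Themes on perceived effect, safety, satisfaction, and willingness to reuse or recommend will then be reported by arm. Themes on procedures and trial experience will be pooled. State that the code numbers in section 6.7 can be traced to the RCT codes in section 5.8, since the protocol does not say whether they are the same.

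The cost is a few wording changes and a short addition to section 6.5, with no extra interviews. The real drawback is that each arm would have only about 12 to 15 transcripts for the treatment-specific themes. Because coding stays blinded, saturation within arm could be examined only after linkage. If it is not reached in one arm, that should be reported as a limitation.

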#### 6.4 Sample size

For the sample size, we will prioritise the study purpose in order to achieve sampling adequacy. The sample size will be expected to be between 24 and 30. In addition, we will estimate the number of participants by data saturation which is defined as no new information having been obtained from the further interview [64]. Therefore, the final sample size will be determined by data saturation.

#### 6.5 Qualitative data analysis

For analysing qualitative data, thematic analysis based on an inductive approach will be conducted [65, 66]. Thematic analysis is described as a flexible approach to analysis that has theoretical freedom, so it is possible to apply a constructivist paradigm and an inductive approach to arrive at a detailed interpretive account of the data [66]. There are six phases of the analytical approach [67]: 1) Familiarization: read and re-read transcripts and field notes to become familiar with the data; 2) generate codes; 3) construct candidate themes; 4) revise themes; 5) define themes; and (6) produce the report. A series of themes and sub-themes will be generated following this process based on grounded theory. All the interviews will be transcribed in full and verbatim by using the original language (Chinese). Transcripts will be de-identified, coded and uploaded to NVivo 12 software (QSR International Version 12, 2018) for data management and data coding [68]. Transcripts will be coded line by line to label themes. Preliminary data analysis will be conducted to determine if the interview guide needs to be revised after every interview.

#### 6.6 Pilot interview

A pilot interview of two participants (one male, one female) will be conducted separately from the main data collection, using the same inclusion criteria. The pilot interview will allow the researcher to develop an interview technique and test the interview guide for validity. Data from the pilot will not be used in the final analysis.

#### 6.7 Data security

The audio recordings of interviews will be transferred to a password-protected computer for storage. Labels of the recording file will be code numbers without identifiable information. Transcriptions of the recording will be completed by researchers using a document which will be stored on a password-protected computer. Transcriptions will be de-identified by using the same code numbers consistent with the recording stored on the computer. The demographic information of participants will be retained on a password-protected computer by researchers. The password for the computer will be known only among the researchers in this study. Field notes and related interview files will be kept in a locked filing cabinet at the GPHCM and RMIT university. Research data will be stored secure for a minimum of seven years at the RMIT and five years at the GPHCM [55]. Only members of the research group and the Ethics committee of the GPCMH will have access to these data. Personal identity of patients will not be disclosed in any public report. We will protect patients' privacy unless required by law.

## **7. Ethics and dissemination**

Ethics approval will be obtained from the Ethics Committee of the GPHCM. The protocol will be registered with the RMIT University Human Ethics Advisory Network. The informed consent form provides details of the research project, it will be signed by the participant and researcher. The participant will be given a copy of the document to keep.

The results of the clinical trial will be published in peer-reviewed journals. All subjects will be required to obtain permission to publish the finding of the trial and to ensure anonymity and confidentiality. All data will be processed under the rules of the government and law. All researchers will guarantee the anonymity of patients and will not disclose the names of patients unless required by law. Only authorized individuals can obtain the patient's information.

